The research team developed the qualitative CSU questionnaire to explore the respondent’s experience while detained and receiving services within a CSU. The qualitative CSU experience questions are designed to assess the participant’s perceived helpfulness and impact from the CSU services which may affect the degree of stabilization respondents feel after discharge from the CSU. The Qualitative CSU experience is a five-item qualitative questionnaire. Qualitative CSU experience is a short survey containing both yes/no and open-ended qualitative questions. The questionnaire asks about the history of admission into CSUs, services received while at CSUs, and several questions regarding the participant’s opinion of their CSU stabilization experience. These opinion questions include what was helpful during their stay, what was not beneficial, and what they would like to change about the program.

The research team developed the Qualitative Technology Use questionnaire to capture the respondents’ opinion on and use of the behavioral health mobile applications. The Qualitative Technology Use is a short four-item survey and contains qualitative and quantitative questions. The questions are designed to address the feasibility and acceptability of the incorporation of mobile applications into our intervention. To do so, questions assess the frequency of use and what participants like and do not like about each app they use. Both treatment and control participants will be asked if they currently use mobile applications to assist with mental, behavioral, or substance use symptoms/treatment. Treatment group participants will be asked if they use any of the recommended apps or any other mobile apps they may use for behavioral health, mental health, and substance use assistance.

Our partnering mental health agency will collect administrative data to record any points of contact or engagement with participants. Administrative data will include re-admissions into CSUs, CSU admission and discharge criteria, number of contact attempts by the mental health agency, type and number of services offered to the participant, and engagement in and retention in acute and long-term treatment by the participant.

The Lawbreaking assessment is a 10-item questionnaire that is a dichotomous “yes” or “no” survey in which participants are asked about lawbreaking behavior. The Lawbreaking assessment was created by the research team and is based on two self-reported crime surveys [53, 54]. The measure asks if they had contact with police, if they participated in an activity that would have resulted in legal consequences had they been caught, or if they failed to pay child support.

The Police-Community Interaction Survey [55] is a 30-item survey that captures reported interactions between respondents and law enforcement. The survey includes dichotomous “yes” or “no” questions where respondents identify if the police officer did a specific action and intensity scales ranging from 1 to 4, where higher reports indicate more satisfaction with the police interaction. The measure has good reliability with subscales above >0.70 and construct validity [55].

#### Data collection

Data collection with recruited participants in the treatment and control groups will occur approximately four times throughout participation. The baseline interview will be conducted immediately following enrollment and consent before the participant discharges from the CSU. The remaining three data collection points include the complete data collection toolset. The first data collection sessions (T1) will occur 2 weeks post-discharge from the CSU. The second data collection point (T2) will be 3 months post-discharge from the CSU. Lastly, the third data collection session with recruited participants will occur 6 months post-discharge from the CSU (T3). These data collection sessions will be conducted at the participant’s home or a nearby public location that the participant requests.

Data from recruited participants will be collected using validated assessment tools, qualitative surveys, and administrative data. These data collection methods will be consistent throughout T1–T3 sessions for the mobile and technology-assisted group and the standard services group. However, the qualitative CSU experience survey may vary based on the participant’s situation. Specifically, the CSU experience survey will be collected only at the T1 interview unless a participant is readmitted to the CSU. If a participant is readmitted to the CSU, the CSU experience survey will be re-asked at the data collection interview following the CSU admission.

Administrative data will be collected for 6 months following enrollment. Additional administrative data will be collected from law enforcement agencies to identify arrests and police contact of participants. Although we will not be assessing for causality in the current proposal, it is critical for us to pilot the collection of these data as they are integral to the follow-up multi-site RCT.

#### Analysis strategy

Data collected from the Mobile and Technology-Assisted Aftercare and Standard Services Groups will allow researchers to gather preliminary data comparing those that receive standard CSU services to those that receive CSU services plus the mobile and technology-assisted aftercare support. Patterns will be monitored to assess the primary and secondary outcomes listed in Table 3. A mixed-data analysis plan, including descriptive statistics (means, proportions, frequencies, and percentages) and bivariate analyses, will be used to capture the range of qualitative and quantitative data present in this study’s primary and secondary outcomes. The study is not designed to detect differences in clinical outcomes; thus, the focus of the analysis provides preliminary information on trends in outcomes and some potential underlying contributors to those trends. These data will provide essential information for advancing knowledge of CSUs and information necessary to inform the future RCT. Qualitative data related to the primary outcomes will be analyzed using the approach described in the Aim 1 analysis strategy. Quantitative analysis for primary outcomes will be conducted using a comparative analysis both within groups and across time. The bivariate analysis will be used to assess correlations and regressions. Additionally, preliminary ANOVAs will be used to assess the trends of participants. Qualitative and quantitative data will be combined using a sequential mixed methods design. Equal weight will be given to the qualitative and quantitative data sources. Data will be reviewed and analyzed for any significant variations that can help assess trends in participants over time and across groups through mean comparison tests.

Mixed methods analysis will be used to assess both primary and secondary outcomes. We will integrate the findings from each of the quantitative and qualitative components [56] by conducting comparative analyses both within and across groups, over time, so that we may examine differences at the county level in terms of quality and fidelity of the intervention. Data will be integrated with quantitative outcome measures, fidelity data, and qualitative interviews using a sequential mixed methods design with equal weight given to qualitative and quantitative data sources [56, 57]. Data will be assessed for significant variations, and qualitative data is used to help us understand quantitative data trends when warranted.

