#### Sample

The goal for Aim 2 is to recruit 24 adults; 12 individuals in the mobile and technology-assisted aftercare group and 12 individuals in the standard services group. These adults will be recruited equally across the three participating jurisdictions resulting in eight participants per county. Individuals brought to the CSU by law enforcement will be randomly assigned to one of two study conditions in equal proportions. To be eligible for participation in Aim 2, individuals must be age 18 or older, English speaking, will discharge to one of three participating counties and plan to remain in the county for 6 months, admitted to the CSU through law enforcement, consent, and the cognitive capacity to understand study participation and to consent. This sample size is strategically small due to testing the feasibility of accessing the needed sample size for future studies. With this pilot sample size, we will be looking at the feasibility of recruiting individuals in a vulnerable, highly transient, population, and retention trends. Both feasibility of recruitment and retention trends will impact our decision on a larger sample size in the subsequent RCT.

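### Repeated scale scores on 24 participants are assigned to bivariate analyses, ANOVAs and mean comparison tests without making the participant the unit; a random-intercept model is a cheap improvement

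*Protocol article*

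**What the plan says.** Under Aim 2, Sample, the target is 24 adults, 12 per arm. Under Aim 2, Data collection: "Data collection with recruited participants in the treatment and control groups will occur approximately four times throughout participation". After the baseline interview, "The remaining three data collection points include the complete data collection toolset"; these are T1 (2 weeks), T2 (3 months) and T3 (6 months).

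Under Aim 2, Analysis strategy, the quantitative methods are descriptive statistics plus the following: "The bivariate analysis will be used to assess correlations and regressions. Additionally, preliminary ANOVAs will be used to assess the trends of participants". Significant variations are then sought that can "help assess trends in participants over time and across groups through mean comparison tests". The section mentions comparison within groups and across time. It names no paired test, repeated-measures ANOVA, mixed model or participant effect. It also does not say that visits are pooled or treated as independent.

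The same section states that the study is not designed to detect differences in clinical outcomes. Even so, Measures plans to use the secondary outcomes to look at effect size and sample size. Aim 3 study design uses Aim 2 data for sample size, and its first progression criterion asks whether the pilot suggests positive effects in the treatment group.

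**The concern.** Three or four scores from one person are correlated, so 24 people do not supply 72 independent observations. A bivariate method relates two variables at a time and cannot hold arm, visit and participant together. An ANOVA or a mean comparison test can be run with or without a participant term, and the text does not say which.

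The choice matters in two ways. Ignoring the link between a person's visits gives wrong standard errors: too small for an arm difference or a correlation computed on pooled rows, too large for change over time. Respecting the link through classical repeated-measures ANOVA gives right standard errors, but only for people with every visit. The protocol itself expects follow-up to be difficult: "With this pilot sample size, we will be looking at the feasibility of recruiting individuals in a vulnerable, highly transient, population, and retention trends". At stake is how firmly the pilot's trends can be read when the future RCT is sized and the first progression criterion is judged.

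**Working it through.** The protocol states no significance level, standard deviation, within-person correlation or standard error, so there is no figure of its own to reproduce. The check asks what each reading of the text would imply.

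**Inputs from the protocol:** 12 per arm (Sample); m = 3 visits with the complete toolset (Data collection); 30.4% average dropout from in-person substance use treatment and about one in five from outpatient mental health treatment (Introduction, CSU aftercare services).

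**Assumed:** within-person correlation ρ of 0.3, 0.5 or 0.7, equal between all visits; two-sided 5% level; normal outcomes; complete data in steps 1 to 3. Simulated figures use 20,000 runs.

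**Step 1. Arm difference or correlation on 72 pooled rows.** The reported standard error of the arm difference is the true one times 1/√(1+(m−1)ρ). The false-positive rate is then about 2[1−Φ(1.96/√(1+2ρ))]. For the correlation of two unrelated measures, each with the same ρ, ρ² replaces ρ. At ρ = 0.5 this gives 1.96/√1.5 = 1.60, or about 11%.

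**Step 2. Visits compared as separate samples.** The reported standard error of a within-person change is the true one times 1/√(1−ρ), so the test is too cautious and loses power.

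| Three visits | ρ = 0.3 | ρ = 0.5 | ρ = 0.7 |
|---|---|---|---|
| Arm SE, reported/true | 0.79 | 0.71 | 0.65 |
| Arm test false positives, formula | 12% | 17% | 21% |
| Arm test false positives, simulated | 12% | 17% | 21% |
| Pooled correlation false positives, simulated | 7% | 10% | 17% |
| Time-change SE, reported/true | 1.20 | 1.41 | 1.83 |
| One-way ANOVA over visits, false positives | 1.6% | 0.4% | 0.06% |
| Arm-by-visit, no participant term, false positives | 1.7% | 0.4% | 0.02% |
| Power, 0.5 SD change between two visits, n = 24, unpaired | 38% | 36% | 32% |
| Same, paired | 51% | 65% | 85% |

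**Step 3. With the participant as the unit.** Testing arms on participant means, and time by repeated-measures ANOVA or a paired test, returns the simulated false-positive rate to about 5% at every ρ.

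**Step 4. Classical repeated-measures ANOVA with missing visits.** Only participants with all three visits contribute. The protocol gives no expected rate of missed interviews. If it equalled the 30.4% treatment dropout, 24 × 0.304 = 7.3, so about 7 would be dropped and 17 kept. At one in five, 24 × 0.2 = 4.8, so about 5. Both are dropout rates from treatment, not from research interviews, and serve only as illustrations.

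Figures for four visits are left out because the complete toolset is stated only for T1 to T3.

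**The case against.** The strongest objection is that the defect is read from silence. ANOVA and mean comparison tests are families that include repeated-measures ANOVA and paired tests, and the section does speak of comparison within groups and across time. With repeated-measures ANOVA, paired tests over time, arm contrasts one visit at a time and correlations within a visit, none of the errors in steps 1 and 2 occurs. The exact form might also be expected in a fuller document that is not shown. This stands to a large extent: a reader might infer that the plan pools visits or that its trend errors are wrong in both directions, but the text does not say so. A time trend analysed as separate samples errs only towards caution. The opposite error belongs to arm tests and correlations on pooled rows.

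Several further limits also stand. With complete balanced data, pooling leaves the estimated arm difference unchanged and distorts only its standard error. With complete data, repeated-measures ANOVA and a random-intercept model give essentially the same inference. The first progression criterion carries no significance threshold. A reader might also infer that the named methods cannot yield the within-person correlation, but a T1–T3 correlation or the repeated-measures mean squares would give it; the plan just does not commit to reporting it.

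What does not stand is that nothing remains to improve. The article names its methods rather than deferring them. Even the favourable reading has a cost: complete-case loss under classical repeated-measures ANOVA, in a sample of 24 from a population the protocol calls highly transient. Separate tests at each visit are valid but do not give the arm-by-visit contrast that a trend over time and across groups calls for.

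**Conclusion.** The point holds as a cheap improvement, not as an error in the plan as written. The named methods leave open whether the participant is the unit. If visits were treated as independent, pooled arm tests on three visits would have a false-positive rate of about 12% to 21% and time trends would be too uncertain. These figures depend on the assumed correlation of 0.3 to 0.7 and a 5% level. If the ANOVAs are classical repeated-measures ANOVAs, those errors vanish and the loss is of participants with an incomplete series, in unknown number.

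The reach is limited. The primary outcomes in Table 3 (recruitment, retention, sessions completed, qualitative acceptability) are not repeated scale scores. The effect is on the secondary outcomes, and through them on the precision attached to the effect estimates used for the RCT design and the first progression criterion.

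**What to change.** In Aim 2, Analysis strategy, state that the participant is the unit of analysis. For each quantitative scale collected at T1 to T3, use a linear mixed model with fixed effects for arm, visit and arm-by-visit and a random intercept per participant, fitted to all available visits. Report the arm difference at each visit and the within-person correlation, each with a confidence interval; the latter is a useful input for sizing a longitudinal RCT. Compute correlations between measures within a visit or on person means, not on pooled rows.

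The cost is a few sentences and a little more programming, with no new data or participants. With 24 people, only a simple random-intercept structure can be fitted.

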#### Measures

Measures for the Mobile and Technology-Assisted Aftercare Group and Standard Services Group include administrative records and direct data collection from participants. The primary outcomes for this feasibility study are participant recruitment, participant retention, feasibility, and the acceptability of the intervention. Participant recruitment will be measured by the number of eligible participants who consent to participate out of the total number of eligible participants. Participant retention will be measured by the proportion of the intervention completed by participants. Feasibility and accessibility will be assessed by triangulating the qualitative and quantitative data from study participants—the CSU professionals and patients.

 The secondary outcomes include individual stabilization and well-being, frequency of both acute and long-term treatment use, re-admission to a crisis stabilization unit, and arrest rates or re-encounters with law enforcement. The secondary outcomes will be assessed to find trends that will inform the future RCT. We will examine the feasibility of collecting the data, the sensitivity of the measures, estimates for effect size and sample size, and other factors that may impact the ability to detect outcomes. For the pilot study, the secondary outcomes are not meant to measure impact; instead, they are intended to examine trends in outcomes to inform the design of the intervention and study protocol for the future RCT. Secondary outcomes will be measured using screening questions, demographical information, clinical assessment tools, and baseline and follow-up interviews with each participant. Administrative data from the CSUs and law enforcement will be collected on client characteristics, including demographics (e.g., race, gender, age, county of residence), criminal history (e.g., current reason for law enforcement contact, prior arrests, and reasons for arrest, and prior CSU stays), and behavioral health status (e.g., diagnoses, prior and current treatment utilization, and medication-assisted treatment). Table 3 shows the measures related to each secondary outcome described below.

**Table 3 Tab3:** Primary and secondary measures

**Primary outcomes**	**Measures**
Participant retention	Number of recruited participants who complete the intervention
Participant recruitment	Number of eligible participants who agree to participate out of the total number of eligible participants

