### Aim 3 study design

#### Aim 3: Design a multi-site RCT to compare the relative impact of CSUs with mobile and technology-assisted aftercare to CSUs without mobile and technology-assisted aftercare

The goal of Aim 3 is to design a large-scale multi-site RCT to compare CSUs with and without mobile technology-assisted aftercare on short and long-term outcomes. It is anticipated that the outcomes in this future RCT will include individual stabilization post-crisis, arrest rates, use of acute services, and increased engagement with long-term treatment

To reach Aim 3, the qualitative data from CSU stakeholders in Aim 1, and data from the pilot trial of the CSU aftercare intervention in Aim 2, will be synthesized to inform and develop a study protocol for the future large-scale RCT. Following the guidelines from the CONSORT extension to pilot trials, data from Aims 1 and 2 will be used to inform the feasibility and suggest critical areas where further development or modification may be required [58]. For instance, data from Aim 1 will explore barriers and facilitators to intervention implementation for agencies and the perceived acceptability of the intervention for our target population and stakeholder procedures. Analysis of Aim 2 data will inform sample size details, referral, appropriate randomization procedures, retention and attrition challenges, and whether randomizing to follow-up mobile supports is the correct variable to randomize on or if there is another more appropriate randomizing variable. Prespecified progression criteria will be assessed from our pilot study to determine whether to proceed with the development of the future RCT. Our progression criteria include the following: (1) do the results of the pilot study suggest positive effects on the treatment group?; (2) did feedback from participants and stakeholders demonstrate the feasibility and acceptability of the intervention?; (3) can a future RCT feasibly be implemented?; and (4) are there potential future partners for a future RCT?

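### The Aim 2 pilot disclaims power for clinical outcomes, yet plans to search 24 people for significant differences and to take effect-size estimates for the future RCT from the same data

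*Protocol article*

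**What the plan says.** All references are to the protocol article.

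- **Size.** Aim 2, Sample, sets a target of 24 participants, 12 per arm, with people "randomly assigned to one of two study conditions in equal proportions". The justification is feasibility: "This sample size is strategically small due to testing the feasibility of accessing the needed sample size for future studies". No significance level, power or target difference is given.
- **Disclaimers.** Aim 2, Analysis strategy: "The study is not designed to detect differences in clinical outcomes". The Measures section says the secondary outcomes serve to show trends and not to measure impact, and the Data collection section says causality will not be assessed.
- **Planned tests.** The same Analysis strategy says that "preliminary ANOVAs will be used to assess the trends of participants", mentions correlations and regressions, and states: "Data will be reviewed and analyzed for any significant variations that can help assess trends in participants over time and across groups", by mean comparison tests. Its second paragraph repeats the search for significant variation.
- **Use for the RCT.** Among the things to be examined with the secondary outcomes, Measures lists "estimates for effect size and sample size". Aim 3 study design adds: "Analysis of Aim 2 data will inform sample size details".
- **Use for the decision to proceed.** The first of four progression criteria (Introduction and Aim 3 study design) asks whether the pilot results suggest benefit in the treatment group.

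**The concern.** The disclaimers and the methods pull in opposite directions. Looking for significant differences over time and between groups is hypothesis testing, whatever it is called, and a study not built to detect differences gives such tests little meaning. Offering effect-size estimates for sample-size planning likewise treats a very imprecise number as information.

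What is at stake is the product of Aim 3. If the observed effect feeds the RCT's target difference, a favourable chance error gives an RCT that is too small. An unfavourable one gives an RCT that is too large, or weighs against the first progression criterion. The primary feasibility outcomes are not affected.

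**Working it through.** **Plan's own figure.** The sample size has no power inputs, so only its arithmetic can be checked: 12 + 12 = 24, and 3 counties × 8 = 24. Both agree.

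**Inputs.** n = 12 per arm (Aim 2, Sample). Two-sided alpha of 0.05: assumed. Standardised differences d of 0.30 to 0.40: the range of four of the five effects quoted from the app meta-analysis in the section on CSU aftercare services (anxiety 0.30, stress 0.35, quality of life 0.35, general distress 0.40; depression is printed as .028 and left out). These are not design values for this trial, whose intervention also includes in-person sessions, so larger values are shown too.

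**1. Precision and significance threshold.** SE of d near zero = √(2/12) = 0.408. With 22 degrees of freedom t = 2.074, so 2.074 × 0.408 = 0.847. An observed d must exceed about 0.85 to be significant, and the 95% interval is about ±0.85.

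**2. Power (noncentral t, 22 df, noncentrality d × √(12/2)).**

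| True d | Power |
|---|---|
| 0.30 | 11% |
| 0.35 | 13% |
| 0.40 | 16% |
| 0.50 | 22% |
| 0.80 | 47% |
| 1.20 | 80% |

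**3. Exaggeration.** In simulated pilots, estimates that reached significance averaged |d| of about 1.04, 1.05 and 1.06 at true d of 0.30, 0.35 and 0.40. The ratios are 1.04/0.30 = 3.5, 1.05/0.35 = 3.0 and 1.06/0.40 = 2.7.

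**4. False positives, illustration only.** Table 3 lists 12 quantitative scales and 2 administrative measures. If each scale were compared between arms at the three follow-ups and each administrative measure once, there would be 12 × 3 + 2 = 38 tests. With every null true, 38 × 0.05 = 1.9 would be expected to be significant. This expectation does not need the tests to be independent. The plan does not specify these 38 tests.

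**5. Sizing the RCT from the observed d.** For 80% power, n per arm = 2 × (1.96 + 0.8416)² / d² = 15.70 / d². At d = 0.35 this is 15.70 / 0.1225 = 128.1, so 129 per arm; at 0.30 it is 175 and at 0.40 it is 99. Now put the pilot's observed d into the same formula, with true d = 0.35 (200,000 simulated pilots of 12 per arm):

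- The chance of an observed d at or below zero is Φ(−0.35/0.408) = Φ(−0.857), about 20%.
- Among the other pilots, the interquartile range of the computed RCT size is 34 to 280 per arm with the small-sample correction to d, and about 32 to 262 without it.
- 61% of those pilots give fewer than 129 per arm, and 44% give fewer than half of it.
- The median true power of the resulting RCT is 60%, not 80%.

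**6. First progression criterion.** Read as any positive observed difference on one outcome, it is met about 50% of the time with no effect and missed about 20% of the time at true d = 0.35.

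**The case against.** The strongest reply is that the article already says what a pilot should say: trends only, no impact, no causality, not designed to detect differences. It also plans descriptive statistics, states no significance level and claims no efficacy. The effect-size phrase sits in a list of things to be examined, and Aim 2, Sample names recruitment and retention as inputs to the RCT size. Nothing says the RCT will be powered on the observed effect alone. The first progression criterion is one of four with no stated veto, and the Discussion ties going ahead to feasibility and acceptability. All of this stands and limits the point. It does not remove the conflict, because the significance search appears twice and the effect-size use is explicit.

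A reader might infer four stronger claims that the document does not support:

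- **Most significant findings will be false.** That holds only if fewer than 0.05/(0.05 + power) of the outcomes truly differ: 32% at d = 0.30 and 24% at d = 0.40. No such share is given. If all 38 illustrative tests had d = 0.30, about 38 × 0.11 = 4.2 would be significant and none would be a false positive.
- **At least one false positive is nearly certain.** High familywise figures need independent tests. Related scales repeated in the same 24 people are not independent, and some Table 3 measures, such as trauma history, are unlikely targets for a comparison at every visit.
- **Participants who miss a visit will be dropped.** The article does not say the ANOVAs are repeated-measures, and model form and missing data are commonly left to a fuller document.
- **RCT measures will be chosen by significance.** The article does not say so, and it already names the anticipated RCT outcomes.

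**Conclusion.** The point holds as an internal conflict with a measurable consequence. Tests and effect-size estimates are planned on clinical outcomes in a sample that the article itself says cannot support them. With 12 per arm and true differences of 0.30 to 0.40 SD, 84% to 89% of real effects would be missed on any single comparison, and significant estimates would be about 2.7 to 3.5 times too large. Some false positives are likely if many measures and visits are tested. An RCT sized on the observed effect would vary about eightfold across the middle half of the pilots that point the right way (280/34 = 8.2).

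The figures rest on two-sided alpha of 0.05, approximately normal outcomes, full retention of 12 per arm and effect sizes borrowed from the cited app literature. Attrition would make them worse: at 8 per arm, power at d = 0.35 is 10%. The RCT sizing result applies only as far as the observed effect is used as the target, which the article allows but does not say is the only input. The correction should be made because it protects what Aim 3 is meant to deliver; participants and the primary feasibility outcomes are not touched.

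**What to change.** 1. **Aim 2, Analysis strategy.** For clinical outcomes, replace both statements about significant variation, the mean comparison tests and the ANOVAs with per-arm summaries at each visit and between-arm differences with 95% confidence intervals. State that no conclusion rests on p-values.
2. **Aim 2, Measures, and Aim 3 study design.** Remove the pilot effect size as an input to the RCT sample size. Base the target difference on a smallest important difference. Take from the pilot only the SD, event rates, the correlation of follow-up with baseline, and retention. Use the upper confidence limit of the SD: with 22 degrees of freedom the 95% limits are 0.77 and 1.42 times the estimate.
3. **Progression criterion 1 (Introduction and Aim 3 study design).** Reword it so that it does not depend on the observed direction or significance of effects in 24 people.

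The cost is wording only; data collection does not change. The downside is that no p-values are reported and the planned RCT may look larger.
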